## Measured Outcomes

Our primary hypothesis is that a regular exposure to *Zeitgebers* stabilizes circadian behavioral rhythms and thereby reduces the risk of alcohol relapses in AUD patients. Therefore, the first primary outcomes of the study are the Routine Variability Score and drinking behavior of each individual test person. For generation of the Routine Variability Scores, first, day-to-day variability will be calculated from the following parameters: bedtime, wake-up time, sleep quality, time of getting-up in the morning, time to go to bed in the evening, lights-off time, breakfast time, lunch time and dinner time. The individual Routine Variability Score is comparable to the validated social rhythm metric scale (SRMS) (66) and will be calculated as follows (example for bedtime): For the period of 1 week, the average bedtime will be calculated. Then the deviation from this average bedtime is calculated in minutes for each day. These deviations are summed up and the mean value is calculated. This mean value will be coded according to the magnitude of time variability: 1: 0–15 min, 2: 16–30 min, 3: 31–45 min, 4: 46–60 min, 5: 61–75 min, 6: 76–90 min, 7: 91–105 min, 8: 106–120 min, 9: 2–3 h, 10: 3–4 h, 11: over 4 h (67). This way a separate score can be created for each parameter collected in the diary. These scores can be calculated on a weekly basis to examine whether relapses or deterioration in well-being are related to irregularities in the daily routine during that week, or over the duration of the entire survey phase to check how regularity over a longer period is related to drinking behavior and well-being. In addition, the scores for sleep and meals, for example, can be calculated individually to examine their influence on drinking behavior and well-being separately.

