## Data Analysis

All statistical analyses will be performed using SPSS software version 25 (SPSS INC., Chicago, IL, USA). Sociodemographic data, chronotype, diary data and blood parameters will be reported in form of descriptive statistics. Continuous variables will be presented as mean ± *SD* and normality of continuous data will be measured by using the Kolmogorov-Smirnov-Test. Accordingly, we will use parametric and non-parametric analyses. For all calculations, the significance level will be determined at α < 0.05.

Data analysis will be performed according to intention-to-treat analysis (ITT) rules. In particular, this means that all subjects who completed the questionnaires of the first session and the 1st week of the diaries are included in the analysis, regardless of whether their subsequent data sets are complete or whether they have dropped out of the study. This is done by imputing missing data with the help of all available data that was assessed until then. Participants who withdraw their consent and were not assessed with baseline measurements will be treated as dropouts. All other subjects regardless from the study condition will be analyzed according to ITT.

The data will be evaluated in three different ways: First, outcomes of the endpoint of the study will be compared between the intervention and control groups using unpaired group analyses (e.g., Student's *t*-test, Mann-Whitney *U*-test, Kruskal-Wallis test, one-way ANOVA). Secondly, within-subject analyses of the intervention and control groups are performed, comparing the changes between the start and end of the study of the two groups (e.g., two-way ANOVA). Thirdly, the data are calculated independently of group membership in two-dimensional linear regression using the Routine Variability Scores as an independent variant.

Additionally, statistical differences in the frequency of dropouts between the two groups are calculated using chi-square tests and survival analyses. Multiple regression analyses will be applied to investigate the degree to which predictor variables (i.e., Routine Variability Scores, depression level, severity of alcohol consumption behavior, and self-efficacy score) contribute to outcomes of primary and secondary measures.

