### Limitations

At this state, however, DAILY has some limitations as it is designed as a pilot study and so, it aims primarily at proofing the principle study concept and the overall impact of a daily structure therapy in AUD patients. A limitation of the current design is that it does not include objective physiological and behavioral measures of circadian rhythm improvement such as (e.g., melatonin rhythms or actigraphy, but only focuses on more subjective behavioral rhythms based on diary entries). However, the primary aim of this pilot study is the proof whether a therapeutic approach to improve sleep hygiene and regularity in daily routine can generally improve AUD symptoms.

Furthermore, inpatients and semi-inpatients are included into our study. Inpatients and semi-inpatients usually already have a more structured daily routine than outpatients since they are given a regulated daily structure by the clinical routines and the fixed therapy hours. Therefore, the determination of individual circadian preferences and characteristics might be limited. However, in our clinic, where the study is currently taking place, patients have no mandatory eating or sleeping hours and can leave the ward and day clinic outside therapy hours. Thus, the test persons can in principle follow their own rhythms, which is often taken advantage of, especially for food and snacks in the surrounding areas. Nevertheless, many test persons report that they generally have more structured daily routines in the clinic than at home, as they adapt to the rhythms of their fellow patients as well as the rhythms of the clinic meals offered.

Furthermore, there are also test persons who, after detoxification or after their stay in the day clinic, go for further treatment to other clinics where they are integrated into a daily structure. Since this daily structure does not necessarily correspond to the subject's circadian characteristics, the analysis of pilot data must consider that these test persons cannot always independently follow the daily schedule during the study. Accordingly, it is possible that the implementation of the DAILY program is more suitable for clinics from which patients are usually discharged home.

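### The Routine Variability Score recodes deviations already measured in minutes into 11 bands, which discards information for no saving; how much power this costs cannot be determined from the article

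*Protocol article*

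**What the plan says.** The Measured Outcomes section states that "the first primary outcomes of the study are the Routine Variability Score and drinking behavior of each individual test person". To build the score, a weekly average time is taken for each parameter (bedtime is the example). "Then the deviation from this average bedtime is calculated in minutes for each day", and the daily deviations are averaged. The average is then banded: "This mean value will be coded according to the magnitude of time variability: 1: 0–15 min, 2: 16–30 min, 3: 31–45 min", continuing in 15-minute steps and ending "8: 106–120 min, 9: 2–3 h, 10: 3–4 h, 11: over 4 h (67").

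The score may be formed per parameter ("This way a separate score can be created for each parameter collected in the diary"), per week or over the whole survey phase, and separately for sleep and for meals. Nine parameters are listed: eight clock times, and sleep quality.

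The Control Group section says the scores will be compared between the arms. The Data Analysis section lists the t-test and the Mann-Whitney test among its examples of unpaired comparisons. It also plans "two-dimensional linear regression using the Routine Variability Scores as an independent variant", and names the scores among the predictors in multiple regression.

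As support for the scale, the article says "The individual Routine Variability Score is comparable to the validated social rhythm metric scale (SRMS"), and it attaches a citation to the bands.

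**The concern.** The minutes exist before the coding step, so the code saves no effort. It only removes detail, in two places.

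- **At the low end.** Everything up to 15 min becomes code 1. The intervention asks patients to keep closely to planned times, so where it works best it moves them into the band where further improvement cannot be seen. The Limitations section adds that "many test persons report that they generally have more structured daily routines in the clinic than at home", so some patients may start near that band.
- **At the high end.** One step is worth 15 min through code 8 and more after that. A linear regression on the code treats all steps as equal, so its slope has no single translation into minutes across the whole scale.

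At stake are sensitivity to the first primary objective, less day-to-day variation, and a pilot's ability to hand an effect and an SD in usable units to the main trial. The Design section gives that second purpose as the reason for the pilot.

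**Working it through.** There is no planned figure to reproduce: the article states no sample size, effect, SD or power. The check therefore has a part that follows from the text and a part that rests on assumptions.

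**1. What the bands do (from the text).** Widths are 15 min for codes 1–8 (8 × 15 = 120 min), 60 min for codes 9 and 10, and open above 240 min.
- A patient going from 14 to 5 min improves by 9 min and moves 0 codes. One going from 16 to 14 min improves by 2 min and moves 1 code.
- From the midpoint of code 9 (150 min) to that of code 10 (210 min) is 60 min, or 60/15 = 4 lower-band steps, yet it counts as one.

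**2. When code 1 is common (assumed: normal daily times, 7 days, absolute deviations).** Deviations are read as absolute because signed deviations from their own mean sum to zero. The expected mean deviation is SD × √(6/7) × √(2/π) = 0.739 × SD. An SD of 20 min gives 14.8 min, just inside code 1. To reach 120 min, where the bands become unequal, needs an SD of about 120/0.739 = 162 min.

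Simulated probability of code 1 in one week, by within-person SD:

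| SD (min) | 10 | 15 | 20 | 25 | 30 | 40 | 60 |
|---|---|---|---|---|---|---|---|
| P(code 1) | 99.9% | 90% | 59% | 32% | 17% | 5% | 0.6% |

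With spread between patients (log-SD 0.5) and a 30% lower SD under DAILY, the share at code 1 (control / DAILY) is about 55% / 75% at a median SD of 20 min, 32% / 53% at 30, 14% / 29% at 45 and 7% / 17% at 60.

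**3. Power on minutes minus power on the code (all inputs assumed).** Two-sided 0.05, 20 or 30 per arm, 30% reduction in SD, log-normal spread between patients, normal or t(3) daily deviations, 2,000 replicates. For scale, the article's 3–5 concurrent participants over 52/6 six-week cycles would give 26–43 patients, or 13–22 per arm, so 30 per arm is on the high side. Ranges run over both arm sizes and both distributions, in percentage points:

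| Median SD (min) | One parameter, one week: rank test | Same: t-test | Mean of 8 parameters × 4 weeks: rank test | Same: t-test |
|---|---|---|---|---|
| 20 | +10.0 to +15.4 | +7.6 to +11.1 | +1.8 to +4.1 | +3.9 to +7.1 |
| 30 | +4.5 to +6.9 | +2.5 to +4.4 | +0.3 to +1.3 | −0.3 to +2.2 |
| 45 | +2.1 to +3.7 | −1.0 to 0 | 0 to +0.8 | −1.4 to −0.7 |
| 60 | +0.5 to +2.0 | −2.7 to −1.5 | −0.4 to +0.4 | −3.0 to −2.2 |

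One example behind the table: SD 20, 30 per arm, normal deviations, one parameter in one week. The rank test has 52.6% power on minutes and 40.4% on the code, a gain of 12.2 points. The Monte Carlo error of one power near 50% is √(0.25/2000) = 1.1 points, so differences of about a point mean little. A second simulation at 20 per arm gave a rank-test gain of 5–9 points at SD 20 for one parameter in one week. The two together give the range of roughly 5 to 15.

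**4. Is a log transform safer?** With log-normal spread between patients, log minutes beat the code in every setting run. With symmetric spread, the averaged log score did worse than the averaged code, by 4–10 points in one simulation and about 15–20 in another.

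**The case against.** A reader might infer that most patients will sit at code 1 and that the arm comparison is materially weakened. The documents do not support that. They give no distribution of deviations, and a majority at code 1 needs a day-to-day SD of about 20 min or less. The Background and Discussion describe patients with irregular routines, meals included. The clinic sets no sleeping or eating hours, and many patients are discharged during the diary weeks. The remark about more structured routines in the clinic is only relative to home.

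Nor do the unequal bands cause a floor. Codes 1–8 are equal; the inequality begins only above a mean deviation of 120 min and affects only the regression slope.

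Other points stand in part:
- The trial is a pilot without a power calculation, so no stated figure is invalidated.
- Rank tests are already allowed and suit an ordinal code.
- The bands carry a citation that cannot be judged here, and keeping a published coding is a legitimate choice.
- A t-test on raw minutes can lose to the code at high variability, because the wide upper bands pull in the right tail.
- Sleep quality is not a clock time, so minutes cannot replace its score.

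What the objection does not touch is that the recode discards information already computed, and that a rank test on minutes was never more than half a point behind a rank test on the code in the table above.

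**Conclusion.** The point holds as an inexpensive improvement, not as a demonstrated loss of power. From the text alone it is certain that changes within 0–15 min cannot register and that one code has no constant value in minutes above 120 min. The size of the loss is not determinable from the documents. Under the assumed inputs (30% reduction in SD, 20–30 per arm) it is roughly 5 to 15 points for a single parameter in a single week when the SD is near 20 min. It is a few points or nil for averaged scores or higher variability, and the t-test on raw minutes can be up to about 3 points worse than on the code. Which of these applies depends on the aggregate analysed, and the article leaves several open. A general claim that log minutes is better would also go too far, since it reverses when the spread between patients is symmetric.

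**What to change.** - For the eight clock-time parameters, make the mean absolute deviation in minutes the analysed Routine Variability measure. Compare the arms with a rank test, which the Data Analysis section already lists.
- Use the minutes as the regressor in the planned regressions, with a log transform only if the data are right-skewed.
- Report arm differences in minutes, which also gives the main trial an effect and an SD it can plan with.
- Keep the 1–11 code as a descriptive summary for comparison with the published scale.
- Leave sleep quality outside this change.

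The cost is a few sentences in the outcome and analysis sections, with no new data, visits or patients. The one small downside is that the primary result is no longer expressed on the published coded scale.

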## Study Design

### Design

The study is a 6-weeks trial with a controlled, randomized, single-blinded, parallel-group design including patients with a diagnosis of AUD. Patients are randomly assigned to either an intervention group (DAILY) or a sham control group (placebo treatment). As this study represents a pilot randomized trial, which does not primarily focus on proving treatment successes but more on ascertaining the best options for the future main trial, we will include each eligible patient within this year instead of using formal power calculations (64).

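### The regressions linking routine irregularity to relapse or well-being omit care setting and study week, so they are open to confounding by discharge

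*Protocol article*

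**What the plan says.** Measured Outcomes offers two uses of the Routine Variability Score. One is weekly: "These scores can be calculated on a weekly basis to examine whether relapses or deterioration in well-being are related to irregularities" in that week's routine. The other uses the whole diary period: "or over the duration of the entire survey phase to check how regularity over a longer period is related to drinking behavior and well-being".

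Data Analysis names two observational models. In the first, "the data are calculated independently of group membership in two-dimensional linear regression using the Routine Variability Scores as an independent variant". The second is a multiple regression with four listed predictors: the score, depression level, severity of drinking, and self-efficacy. Neither contains setting, discharge status or study week. The common threshold is stated as "For all calculations, the significance level will be determined at α < 0.05".

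On setting, the article says the following:
- The background section on the transition from inpatient to outpatient care describes discharge as a period in which daily rhythms become irregular and relapse is more likely.
- The section on weeks 3–6 says many patients are discharged or transferred during that phase, at differing times.
- Limitations reports that "many test persons report that they generally have more structured daily routines in the clinic than at home". For patients who go on to other clinics it adds that "the analysis of pilot data must consider that these test persons cannot always independently follow the daily schedule during the study". It names no term or method, and this instruction does not mention patients discharged home.

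**The concern.** By the article's own account, setting influences both sides of the regression. Being in the clinic makes routines more regular, and leaving it raises the risk of relapse by routes other than meal and sleep times, such as stress and the abrupt return to self-organisation. Setting precedes the week's irregularity, so it is a confounder, and adjusting for it is not over-control. If setting changes while diaries are kept and is left out of the model, weeks or patients with more time outside the clinic tend to show both more irregularity and more drinking, even if regularity does nothing.

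The primary hypothesis is that regular Zeitgeber exposure stabilises rhythms and through this reduces relapse. The score–outcome regressions are the stated analyses closest to that middle step. The pilot is meant to inform a main trial, so an association produced by discharge could be carried forward as evidence of mechanism.

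**Working it through.** The article gives no sample size ("we will include each eligible patient within this year instead of using formal power calculations"), relapse rate or irregularity figure, so there is no stated figure to reproduce. The check has three parts.

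**1. Does setting change within the diary phase?**

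Inputs from the article: ward stay 14 days; ward enrolment after 5 days of detoxification at the earliest; day-clinic stay 2–4 weeks; diary of 7 test days plus 28 application days, 35 in all. Assumptions: a gap of 0, 3 or 5 days between enrolment and the start of the diary, and day-clinic enrolment on admission.

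Diary days in clinic = stay − enrolment day − gap, capped at 35.

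- Ward only: 14 − 5 − 0 = 9; 14 − 5 − 3 = 6; 14 − 5 − 5 = 4. This covers 4–7 test days and 0–2 of the 28 application days.
- Day clinic: from 14 − 0 − 5 = 9 to 28 − 0 − 0 = 28, of which 2–21 are application days.
- Ward followed by the longest day-clinic stay: 42 − 5 − gap gives 35 (capped), 34 or 32.

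So setting shifts from early to late weeks for many patients, but not for all.

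**2. Weekly regression when regularity has no effect**

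Assumptions: half the patients spend one diary week in clinic and half spend 1–4 weeks; mean deviation is 25 min in clinic; patient SD 8 min and weekly SD 12 min; weekly drinking days are binomial (7, p), with p = 2% in clinic and depending on setting only. Drinking days are regressed on deviation by ordinary least squares. The table shows how often p < 0.05.

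| Patients | Deviation outside | Drinking days outside | All 5 weeks | 4 application weeks |
|---|---|---|---|---|
| 40 | 40 min | 8% | 48% | 17% |
| 40 | 40 min | 15% | 87% | 43% |
| 30 | 35 min | 8% | 22% | 9% |
| 40 | 30 min | 8% | 9% | 6% |

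With a setting term the rate is about 5%. Repeat runs agree within about three percentage points.

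The last column matters because of how drinking is measured. The diary items listed for week 1 do not include drinking. The final Timeline Followback reaches back 30 days. If the last session closes the 28 application days, it covers only 30 − 28 = 2 test days and misses 7 − 2 = 5. Mood and craving are recorded daily in the diary, so well-being analyses could use all five weeks.

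**3. A second simulation of different form**

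Assumptions: weekly relapse yes/no, 2% in clinic and 15% after discharge; discharge after week 1–5 at random; standard errors clustered by patient; no true effect. Unadjusted false-positive rates at n = 30 / 60 / 100:

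- Irregularity rises by 0.5 SD on discharge: 8.5% / 12% / 17%.
- Rises by 1 SD: 16% / 34% / 44%.
- Rises by 2 SD: 37% / 71% / 88%.
- Setting moves only one of the two variables: 5–7%.
- With a setting term, all scenarios: 3–8%.

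One whole-phase score per patient is less affected: 4–30% at 2% versus 15% relapse, and up to 53% at 2% versus 25% with n = 100 and a 2 SD shift.

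**The case against.** A reader might infer that the plan pools all weeks into one regression and that the link then appears automatically. The documents do not support either step. Measured Outcomes says scores can be calculated by week or over the whole phase. What Data Analysis explicitly pools is the two groups ("the data are calculated independently of group membership in two-dimensional linear regression"), and it states no unit of analysis. Nor is the bias automatic: it needs setting to move both variables, and in the mildest scenarios the false-positive rate is close to nominal.

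Further points on the other side stand in part:

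- Much of the five-week result comes from the test week, for most of which the article names no drinking measure. It mentions weekly relapses but does not say how they are dated.
- A clean split between clinic and home is too simple. Day-clinic patients arrange evenings and weekends themselves from the start, the ward has no fixed sleeping hours, and some patients move to another structured institution.
- The simulations ignore that the intervention arm follows a plan meant to lower irregularity. Assuming a 10-minute reduction in that arm, the first scenario falls from 49% to 33% over five weeks, and from 20% to 18% over the application weeks (separate runs of the table's first row).
- Limitations acknowledges transferred patients, and a full analysis plan may specify covariates. However, this article does state its models and predictor list, and neither carries out what Limitations says must be considered.
- The between-group comparison is protected by randomisation, and the pilot is not primarily meant to prove efficacy. Both are correct. They limit the consequence to the observational association.

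**Conclusion.** The point holds as a confounding problem in the observational score–outcome regressions. The article supplies every link: setting affects regularity, leaving the clinic brings relapse, setting changes during the diary phase, and the stated models leave it out. An association found with these models cannot be separated from the effect of discharge.

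The size is uncertain. With no true effect, the main simulation gives about 9–87% false positives over five weeks and about 6–43% over the four application weeks, against about 5% after adjustment. These figures rest on assumed sample sizes, drinking rates and irregularity shifts, and on a two-state setting that overstates the contrast for some patients. They show that the bias can be material, not that it will be. The whole-phase analysis is less exposed but not immune. The randomised comparison between DAILY and control is unaffected. The change is worth making before analysis because it is cheap and concerns the analyses most likely to be read as evidence of mechanism.

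**What to change.** - Code setting for each diary week as ward, day clinic, home or other institution, from existing hospital and discharge records.
- In any weekly regression of an outcome on the score, include setting and study week as time-varying terms with a patient effect. Alternatively, analyse post-discharge weeks separately.
- For whole-phase scores, adjust for the share of diary days spent in clinic.
- Add setting to the multiple-regression predictors in Data Analysis, so that the model does what Limitations says must be considered and also covers patients discharged home.
- Report the irregularity–outcome association as exploratory and not as evidence of mechanism.

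The cost is one coded variable and a revised model statement. The slope becomes slightly less precise, because differences between clinic and outside weeks no longer contribute to it.
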